### Intervention

The REACH-HF intervention is grounded in the support needs and priorities of people living with HF and the services that provide care for them. A systematic, six-step Intervention Mapping framework^13^ guided intervention development, drawing on research evidence, national and international guidelines and stakeholder consultations with patients, caregivers and health professionals to identify ‘targets for change’. In line with Intervention Mapping regulatory processes, underpinning target behaviour patterns and evidence-based change techniques were matched to each behaviour-change target.^14^ A key element of the intervention development process was an active Patient and Public Involvement group consisting of six people with a range of experiences with HF and three caregivers of people with HF. The intervention development process is described in detail elsewhere ([name], [name], [name], *et al*. Development of a facilitated self-care and rehabilitation intervention for people with HF and their care givers: Rehabilitation Enablement in Chronic Heart Failure (REACH-HF). Submitted for publication 2015).

The REACH-HF intervention is a comprehensive self-care support programme comprising the ‘Heart Failure Manual’ (HF Manual), with a choice of two exercise programmes for patients, a ‘Family and Friends Resource’ for caregivers, a ‘Progress Tracker’ tool and a training course for intervention facilitators.

Participating patients and caregivers will work through the self-help manual over a 12-week period with facilitation by a specially trained intervention facilitator (cardiac nurse or physiotherapist by background), who will help to build the patient's and caregiver's understanding of how to manage HF. The manual includes information and interactive elements covering a wide range of topics relating to living with/adapting to living with HF, and includes four core elements:
An exercise training programme, tailored according to initial fitness assessments, delivered as a walking programme or a chair-based exercise DVD, or a combination of the two (the patient's choice);Managing stress /breathlessness /anxiety;HF symptom monitoring (and associated help-seeking);Understanding and taking medications.

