Patients will be encouraged to use the progress tracker booklet, which is designed to collect the following information over the period of the intervention: changes in physical and mental state, intensity of exercise and self-reported walking speed, and degree of completion of self-monitoring sections for physical activity, enjoyable activities, frequency of self-weighing (to monitor fluid build-up), and frequency of self-reported use of stress-management techniques. The Family and Friends resource, a manual for use by caregivers, includes advice on providing support, becoming a caregiver, managing caregiver's own health and well-being and getting help.

As a pragmatic trial of a self-help intervention which is reliant on the willing engagement of recipients, there are no specific strategies to improve participants’ adherence to intervention protocol. Intervention delivery may be discontinued at any time at the request of a participant or by the intervention facilitator if they determine that the intervention may be the cause of undue harm.

Adherence to intervention protocols from the perspective of the intervention facilitators will be ascertained through fidelity assessment described herein.

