### Usual care

In accord with findings of our national survey,^9^ patients with HF typically do not receive CR, despite NICE recommendations.^1^ The choice of a usual care (no rehabilitation) comparator in the REACH-HF trial is therefore reflective of the situation for the vast majority of patients with HF. In this trial, intervention and control group patients will receive usual medical management for HF according to national and local guidelines, including specialist HF nurse care. The use of care services, including those provided by specialist HF nurses in the community and in secondary care, will be documented at each follow-up through participants’ completion of healthcare resource use questionnaires and by collection of concomitant medication usage as reported by participants.

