#### Process evaluation study 5: Use of progress trackers to identify patient changes associated with effectiveness

As described earlier, the REACH-HF Manual includes a progress tracker which intervention patients will be encouraged to use to track their progress including physical activity, mood, symptoms and self-care actions. At the end of the intervention delivery period, copies of the participants’ progress trackers will be provided to the research team and digitally scanned. This information together with the number of facilitator contacts and total contact time received, will allow characterisation of individual patient engagement in the intervention. To the extent that this is the case, tracker scores can be used to explore potential changes which indicate likelihood of intervention success.

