The potential for differential intervention effects within patient subgroups (ie, moderation by patient characteristics) will be explored using interactions within linear regression modelling for the primary outcome only. Mediation analyses will be used to assess the extent to which secondary outcomes at intermediate follow-up (eg, self-efficacy or physical activity levels at 4 months) or progress tracker self-care behaviours (eg, self-reported exercise, stress or anxiety management activities) can explain between-group differences in the primary outcome at 12 months. Moderation and mediation analyses will be exploratory in nature as no formal power calculation for interaction effects has been performed.

Serious adverse events will be presented descriptively by treatment arm.

All between group outcome results will be presented as means and 95% CIs. No correction of p values for multiplicity of testing will be undertaken. However, the primary outcome (MLHFQ at 12 months) analysis will be performed before all other analyses and the p values of all subsequent analyses interpreted in the context of multiple testing. No interim analyses will be performed. All analyses will be conducted by a statistician who is blinded to treatment arm, using Stata V.12.

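### Progress-tracker behaviours cannot mediate the between-group difference in MLHFQ, because the protocol describes tracker data for the intervention arm only

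*Protocol article*

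**What the plan says.** **The planned analysis.** In the protocol article, Data analysis, Primary and secondary outcomes, the mediation sentence names two kinds of mediator for the arm difference in 12-month MLHFQ. The first is secondary outcomes at intermediate follow-up, with self-efficacy and physical activity at 4 months as examples. The second is given as "or progress tracker self-care behaviours (eg, self-reported exercise, stress or anxiety management activities) can explain between-group differences in the primary outcome". The same paragraph labels moderation and mediation analyses exploratory.

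**The source of the tracker data.** The Intervention section lists, among the parts of the package, "a ‘Progress Tracker’ tool and a training course for intervention facilitators". It describes the booklet as "designed to collect the following information over the period of the intervention". Process evaluation study 5 says that "the REACH-HF Manual includes a progress tracker which intervention patients will be encouraged to use to track their progress", and then: "At the end of the intervention delivery period, copies of the participants’ progress trackers will be provided to the research team".

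**The control group.** The Usual care section describes "The choice of a usual care (no rehabilitation) comparator". The Trial data collection section lists questionnaires, the shuttle walk, blood samples and accelerometry for participating patients. It mentions no tracker or similar diary.

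**The other stated use of the tracker.** Study 5 says that "tracker scores can be used to explore potential changes which indicate likelihood of intervention success", after describing the tracker as a way to characterise each patient's engagement with the intervention.

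**The concern.** To say that a behaviour explains part of an arm difference, one must know how far the arms differ on that behaviour. The tracker gives its level in intervention patients only. The sentence therefore asks for a between-group decomposition from one-group data, whereas study 5 puts the same data to what is essentially a within-group use.

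Exploring mediators of change in disease-specific quality of life is a listed secondary objective. An analyst following the sentence literally would either find that the model cannot be fitted or would supply a value for controls. The second course gives a direct and an indirect effect that look like evidence on how the intervention works but depend on the value supplied.

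**Working it through.** The plan gives no figure for the mediation analysis, so there is none to reproduce. The only trial number needed is the planned 108 per group from the Sample size section.

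**1. Fitting the model as stated.** Conventional mediation uses two regressions: tracker score on arm, and 12-month MLHFQ on arm and tracker score. Controls have no tracker score, so a complete-case fit drops all of them. Arm is then constant. The design matrix of the second regression (intercept, arm, tracker score) has rank 2 instead of 3. Neither the arm-to-mediator effect nor the direct effect can be estimated.

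**2. Coding controls as zero.** The protocol does not propose this, but it is the obvious way to make the model run. Notation:
- m1 and m0: mean behaviour in the intervention and control arms
- b: change in MLHFQ per unit of behaviour
- d: true direct effect

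The total effect is d + b(m1 - m0), and the true indirect effect is b(m1 - m0). With controls set to zero, all variation in the mediator beyond arm lies within the intervention arm, so its coefficient is the within-intervention-arm slope. A numerical check agreed to better than 1e-13. If that slope is b, then:
- zero-coded indirect effect = b × m1, in error by b × m0
- zero-coded direct effect = total - b × m1 = d - b × m0

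Unless b is zero, the split is right only if m0 = 0.

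**3. Size under assumed values.** The documents give no value for b, d, m1 or m0. Take b = -3, d = -2 and m1 - m0 = 1, with negative values favouring the intervention. The truth is then indirect -3, direct -2 and total -5 in every row.

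| Control mean m0 | Intervention mean m1 | Zero-coded indirect | Zero-coded direct |
|---|---|---|---|
| 0 | 1 | -3 × 1 = -3 | -5 + 3 = -2 |
| 1 | 2 | -3 × 2 = -6 | -5 + 6 = +1 |
| 2 | 3 | -3 × 3 = -9 | -5 + 9 = +4 |

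A simulation of the last row (2000 runs, 85 per arm) gave -9.03 and +4.02 with zero-coding. With the mediator measured in both arms it gave -2.99 and -2.02.

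**4. Self-selection.** Tracker use is voluntary. Suppose an unmeasured factor raises the behaviour by 0.7 per SD and shifts MLHFQ by -4 per SD, with within-arm variance of the behaviour equal to 1 (all assumed). The estimated slope becomes -3 + (-4 × 0.7) = -5.8. With m1 = 3, the zero-coded indirect effect is about -5.8 × 3 = -17.4 (simulated -17.3, with direct +12.31). Measuring the mediator in both arms removes the m0 error but not this confounding: the indirect effect is about -5.8 × 1 = -5.8 (simulated -5.75, with direct +0.76).

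**The case against.** **The analysis is exploratory and the clause is small.** This stands as a limit on importance. The other half of the sentence is sound, and study 4 names exercise capacity, psychological well-being, physical activity and self-efficacy as possible intermediate outcomes, so the mediator objective can be met without the tracker. The label does not cure the defect, however. The reason given for it is the absence of a power calculation for interaction effects, and an effect that the data do not identify stays unidentified at any sample size.

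**Study 5 already describes the sensible use.** This is true, and it makes the repair easy. It also means that the two sections disagree and that the data analysis sentence should give way.

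**The analysis plan may settle it.** The point concerns an analysis that the article states, not a detail that it leaves out. A later plan could put it right only by departing from this sentence.

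**No estimator is named, and zero can be a true value.** This stands in part. For pure uptake measures, such as tracker use itself or number of facilitator contacts, zero in controls is true by design, and methods that use randomisation as an instrument exist under further assumptions. The examples in the sentence are of another kind: controls may also exercise or manage stress.

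**Stronger readings to avoid.** A reader might infer that the whole mediation plan fails; the both-arm mediators show that it does not. A reader might also infer that a zero-filled tracker score nearly duplicates the arm indicator and so inflates standard errors by a known amount. The documents do not support that: they propose no zero-filling and give no mean or SD for tracker scores, and the main harm of zero-filling is bias.

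**Conclusion.** The tracker clause is wrong as written. For self-care behaviours that controls may also perform, the described data do not identify the arm-to-mediator effect or the direct effect, and zero-coding replaces the missing information with an assumption that is unlikely to hold.

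What follows from the text is that tracker data are described for none of the 108 planned controls. The size of the bias under zero-coding is not known. It equals b × m0, and the figures of -3 to -9 for a true indirect effect of -3 illustrate assumed values only. The conclusion also rests on controls having no tracker or equivalent record. The schedule table could not be read, but no text suggests that they have one.

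Importance is modest. One clause of an exploratory analysis is affected. Mediation through 4-month variables measured in both arms, the primary analysis and the sample size are not.

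**What to change.** - Delete tracker behaviours from the between-group mediation sentence.
- Limit that analysis to mediators measured in both arms at 4 months: self-efficacy, SCHFI, accelerometry, ISWT and HADS. Adjust for the baseline value of the mediator and for baseline MLHFQ. The data analysis section already commits to the second adjustment.
- Report tracker data only as an association with outcome within the intervention arm, labelled non-causal, in line with process evaluation study 5.

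The cost is wording only. The both-arm mediators are already collected, and no new data or patients are needed.

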#### Economic outcomes

Means (and SDs) for resource use and costs will be presented for baseline assessment, and for resource use over the 12-month follow-up period. Regression methods will be used to estimate mean costs per group and to compare mean costs between treatment and control groups. MLHFQ data will be drawn from the main statistical analyses. QALY data will be derived from trial data on EQ-5D-5L, using a UK algorithm/tariff, in the first instance those derived from Dolan^34^ (via van-Hout *et al*^35^; although it is expected that a UK tariff will be published at the time of analysis), for the 5-level EQ-5D). Derived health state values will be used to estimate QALYs through application of standard area-under-the-curve methods^36^ using all data from baseline to 12-month. Analysis of mean QALY per group, and differences between groups will be undertaken using regression based methods, adjusting for baseline EQ-5D-5L, and using covariates as the main statistical analyses on effectiveness. As analyses are over a 12-month period no discounting of (future) costs or outcomes is required.

#### Qualitative outcomes

A thematic analysis of interviews will be conducted^37^
^38^ to generate emerging themes and overarching themes.^37^ Other members of the team will conduct independent analyses of subsets of the data, and the qualitative team will meet regularly to discuss coding and analysis. Reflexive notes will also be used to help assure transparency and trustworthiness of the analysis.^39^ The analysis will characterise patients’ observed and self-reported responses to the intervention and link these responses to overall use and perceived benefit, identifying interpersonal and intrapersonal processes that shape effectiveness or ineffectiveness of the intervention. At 4 months, patients’ engagement with, response to and use of the REACH-HF Manual will be characterised and differences between patients noted. At 12 months overall use of and benefit derived from the REACH-HF manual, and maintenance of self-care behaviours and coping skills will be characterised and linked to individual differences in 4-month responses. This will allow a qualitative description of potential pathways and barriers to improvement. Data from the caregiver interviews will be analysed using similar methods.

### Data monitoring and quality assurance

The Site Principal Investigators ([name]) or authorised delegate will check completed CRFs for missing data or obvious errors before the forms are sent to the CTU. Data will be monitored centrally for quality and completeness by the CTU and every effort will be made to recover data from incomplete forms where possible. The CTU data manager will oversee data tracking and data entry and initiate processes to resolve data queries where necessary. The CTU trial managers ([name]) will devise a monitoring plan specific to the study which will include central monitoring strategies and study site visits as appropriate. Participating sites will be required to permit the CTU trial manager or deputy, or representative of the sponsor, to undertake study-related monitoring to ensure compliance with the approved study protocol and applicable standard operating procedures (SOPs), providing direct access to source data and documents as requested. All study procedures will be conducted in compliance with the protocol and according to the principles of the International Conference on Harmonisation Good Clinical Practice (ICH GCP). Procedures specifically conducted by the CTU team (eg, data management, study management and study monitoring) will be conducted in compliance with CTU SOPs.

### Trial management and independent committees

Team members directly involved with the day-to-day running of the trial will meet weekly to discuss trial progress, teleconferencing with site PIs on a monthly basis with email and telephone exchange as necessary between. The Programme Management Group including health economics, statistics, process evaluation and patient and public representation will meet on a termly basis to review status of the overall programme, including trial progress.

The REACH-HF Programme Steering Committee (Chair: [name] and four other independent members including a patient and public involvement representative) have formally agreed to adopt the role of Trial Steering Committee and will oversee the conduct of the trial with safety and ethics review by a fully independent Data Monitoring Committee (Chair: [name] and two other independent members). Evidence for treatment differences in the main efficacy outcome measures will not be monitored through review of accumulating outcome data and no interim data analyses will be conducted.

The Trial Steering Committee and Data Monitoring Committee meet one to two times per year. Detailed descriptions of the remit and function of the oversight committees are documented in specific charters held in the Trial Master File by CTU.

## Ethics and dissemination

The study will be conducted in accordance with the ethical principles that have their origin in the Declaration of Helsinki and that are consistent with ICH GCP, and in accordance with the Research Governance Framework for Health and Social Care, Second edition (2005). The study is sponsored by Royal Cornwall Hospitals NHS Trust (Research, Development & Innovation Department, Royal Cornwall Hospital, [name]). Written informed consent will be obtained from all participants prior to study enrolment. Participants enrolled into the study are covered by indemnity for negligent harm arising from the management, design and conduct of the research through standard NHS Indemnity arrangements. The study is approved by the National Research Ethics Service Committee North West—Lancaster Research Ethics Committee (reference 14/NW/1351). Any subsequent amendments will be made using the Integrated Research Applications System in order to maintain ethical approval and NHS permissions. Amended documents will be provided to investigator sites by CTU. In the event of changes to study design requiring significant amendment to the content of the participant information sheet, participants will be required to provide renewed informed consent.

Findings will be published in peer-reviewed journals and presented at local, national and international meetings and conferences to publicise and explain the research to clinicians, commissioners and service users. A final report will be submitted to the National Institute for Health Research and a summary report will be circulated to NHS commissioners and service providers, patient groups and trial participants. All investigators will have access to the final data set. Participant-level data sets will be made accessible on a controlled access basis.

## Conclusion

This randomised controlled trial aims to assess the clinical and cost-effectiveness of the Rehabilitation Enablement in Chronic Heart Failure (REACH-HF) intervention, a manualised home-based rehabilitation intervention designed to improve self-care and HRQoL in people with systolic HF. We will also assess the outcomes of caregivers. The study results will provide valuable information for clinicians, policymakers, patients and their caregivers about the role of self-directed rehabilitation interventions and has the potential to positively impact on the current dearth in the provision and uptake of rehabilitation services for people with HF and caregiver support.
